## Abstract

**Background:**

Proximal humerus fracture is the third most common fracture type after hip and distal radius fracture in elderly patients. A comprehensive study by Palvanen *et al*. demonstrated an increase in the annual fracture rate of 13.7% per year over the past 33 years. Should this trend continue, the fracture rate would triple over the next three decades. The increasing incidence of low-energy fractures raises questions about the optimal treatment in terms of functional outcome, pain, and rehabilitation time, as well as the economical impact. Despite the high incidence and costs of proximal humerus fractures, there is currently no valid scientific evidence for the best treatment method. Several publications, including a Cochrane review outline the need for high-quality, well-designed randomized controlled trials.

**Methods/Design:**

The study is a prospective, randomized, national multi-center trial. The hypothesis of the trial is that surgical treatment of displaced proximal humerus fractures achieves better functional outcome, pain relief, and patient satisfaction compared to conservative treatment. The trial is designed to compare conservative and surgical treatment of proximal humerus fractures in patients 60 years and older. The trial includes two strata. Stratum I compares surgical treatment with locking plates to conservative treatment for two-part fractures. Stratum II compares multi-fragmented fractures, including three- and four-part fractures. The aim of Stratum II is to compare conservative treatment, surgical treatment with the Philos locking plate, and hemiarthroplasty with an Epoca prosthesis. The primary outcome measure will be the Disabilities of the Arm, Shoulder and Hand (DASH) score and the secondary outcome measures will be the EuroQol-5D (EQ-5D) value, OSS, Constant-Murley Score, VAS, and 15D.

Recruiting time will be 3 years. The results will be analyzed after the 2-year follow-up period.

**Discussion:**

This publication presents a prospective, randomized, national multi-center trial. It gives details of patient flow, randomization, aftercare and also ways of analysis of the material and ways to present and publish the results.

**Trial registration:**

ClinicalTrials.gov identifier: NCT01246167

## Background

Proximal humerus fracture is the third most common fracture type after hip and distal radius fracture in elderly patients [1-3]. Proximal humerus fracture accounts for approximately 4% of all fractures [1-3]. Approximately 85% of the patients are treated conservatively and will regain shoulder function without surgery [4]. Most of these fractures are stable and minimally or non-displaced osteoporotic fractures and they commonly occur in women [4]. The mechanism of low-energy injury in elderly patients is usually falling from standing height. In Finland in 2002, the age-adjusted fracture incidence in persons 60 years and older was 105 per 100,000 person-years [5]. A comprehensive study by Palvanen *et al*. demonstrated an increase in the annual fracture rate of 13.7% per year over the past 33 years [5]. Should this trend continue, the fracture rate would triple over the next three decades.

The increasing incidence of low-energy fractures raises questions about the optimal treatment in terms of functional outcome, pain, and rehabilitation time, as well as the economical impact. Despite the high incidence and costs of proximal humerus fractures, there is currently no valid scientific evidence for the best treatment method. Several publications, including a Cochrane review outline the need for high-quality, well-designed randomized controlled trials. The challenge for the future is to determine which patients will benefit from surgery and to establish surgical techniques that produce optimal results for each fracture type. The aim of this randomized controlled trial is to evaluate whether the outcome in patients over 60-years of age with displaced two-, three-, and four-part fractures of the proximal humerus is improved by surgical intervention.

### Diagnosis and treatment

Diagnosis of proximal humerus fracture is based on clinical and radiologic findings and the mechanism of injury. A standard set of three radiographs from different views is generally obtained. The Neers’s or AO (Arbeitsgemeinschaft für Osteosynthesefragen) classification systems are widely used to define these complex fractures [6]. Although these systems have been used extensively for many decades, their reliability has been challenged. The AO system categorizes the fracture types into 27 fracture patterns, making its use labor- and time-intensive and complicated (Müller 1990). The Codman-Hertel binary fracture description system does not address the fracture pathomechanism (Hertel 2004). The Codman-Hertel system was improved by Resch by adding the pathomechanism of the fracture to the classification [7]. In all classification systems, however, the intra- and inter-observer agreement are graded as poor or, at best, moderate [8]. Due to poor intra- and inter-observer agreement of the Neer’s or AO classification systems, various radiographic protocols have been introduced to improve the diagnostic reliability of the classification. CT is often performed to facilitate treatment decisions.

Approximately 15% of patients with proximal humerus fracture are treated surgically [9]. Several fixation methods have been introduced, including Kirschner-wire fixation, screw fixation, plate fixation, intramedullary fixation, and prosthesis [10]. Currently, the locking plate system is the most frequently used method for fixation in two- and three-part fractures and a locking plate or prostheses is often used in displaced three- and four-part fractures in elderly patients [11]. With locking plates, the normal anatomy may be restored and the range of motion (ROM) is reported to recover up to 80% to 85% that of the healthy side [10,12]. The disadvantage of the locking plates includes a rather high complication rate of up to 49% [13]. A stable and usually pain-free shoulder is achieved with a prosthesis, but recovery of ROM is poor [10,12,14-17].

### Evaluation of treatment

Tools that are widely used for measuring the mobility and usability of the shoulder include the Constant-Murley score; Disabilities of the Arm, Shoulder and Hand (DASH) questionnaire; Oxford Shoulder Score (OSS); and Visual Analog Scale (VAS). In addition, the EuroQol-5D (EQ-5D) and 15D questionnaires survey the patient's general quality of life through different questions pertaining to various areas of life and are widely used in medical trials [18]. The outcomes are indexed and are comparable with reference populations as well as with the patient's own results in other stages of the treatment. Finnish versions of the EQ-5D and 15D have been validated [19,20].

### Previous studies

Although the literature on proximal humerus fractures is extensive, the majority of studies lack randomization, comparators, and independent evaluation, which makes it impossible to draw clinically meaningful conclusions [21]. Recent publications include three well done randomized, controlled trials. Olerud *et al.* carried out randomized controlled trials on three-part fractures, comparing nonsurgical treatment with angle-stable plates in elderly patients. The results indicated advantages in functional outcome and health-related quality of life favoring the locking plate, but the clinical significance remains unclear [22]. Fjalestad *et al.* studied displaced three and four-part fractures in patients over 60 years of age. They found no evidence that surgical treatment with an angle-stable device provided better results than conservative treatment [23]. Others have reported conflicting results. Olerud *et al.* studied displaced four-part fractures in elderly patients. They compared hemiarthroplasty and conservative treatment and found that arthroplasty provided a significant advantage in terms of quality of life. The main advantage was less pain although there was no difference in ROM [24].

In 2009, Hanson *et al.* published functional results of 160 patients treated conservatively. After a 12-month follow-up, the difference compared to the healthy side was 8.2 points measured with the Constant-Murley score. The difference in the DASH score was 10.2 points, which is below the minimal detectable change. Non-union risk was 7.0%, with smokers having a 5.5 times greater risk than nonsmokers [25].

The updated Cochrane meta-analysis published in 2010 was unable to provide guidelines for treating proximal humerus fractures due to a lack of solid evidence. Three- and four-part fractures in patients over 60 years of age are especially challenging as scientific consensus on their treatment has yet to be established [21].

## Methods/Design

The present randomized controlled trial is designed to compare conservative and surgical treatment of proximal humerus fractures. The trial includes two strata. Stratum I compares surgical treatment with locking plates to conservative treatment for two-part fractures. Stratum II compares multi-fragmented fractures, including three- and four-part fractures. The aim of Stratum II is to compare conservative treatment, surgical treatment with the Philos locking plate (Synthes®), and hemiarthroplasty with an Epoca prosthesis (Synthes®).

### Hypothesis

The study is a prospective, randomized, national multi-center trial. The hypothesis of the trial is that surgical treatment of displaced proximal humerus fractures achieves better functional outcome, pain relief, and patient satisfaction compared to conservative treatment in terms of ROM, and Constant-Murley, DASH, OSS, EQ-5D, 15D, and VAS scores. Subgroup analysis will be performed in an effort to obtain limit values for specific treatments of different age and fracture groups. In addition, we hypothesize that shoulder function will improve for up to 1 year from the time of fracture, and after 1 year significant improvement will be arrested [26]. The primary outcome measure will be the Disabilities of the Arm, Shoulder and Hand (DASH) score and the secondary outcome measures will be the EuroQol-5D (EQ-5D) value, OSS, Constant-Murley Score, VAS, and 15D.

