### Follow-up

Follow-up will be carried out at the orthopedic outpatient clinic of the hospital where the patient was primarily treated. The patients will visit the outpatient clinic at 6 weeks and 3 months. Ultrasound examination of the fractured shoulder to assess possible rotator cuff injury will be performed at the 3-month visit by an experienced musculoskeletal radiologist.

Orthopedic outpatient clinic visits will be continued if necessary. In addition to these visits, in each center a blinded physiotherapist or sports physiologist will perform a research examination at 6 months, and 1, 2, 5, and 10 years from the beginning of the treatment. Patients are supposed to wear a shirt to blind the examiner. During these visits, radiographs will be taken of the treated shoulder, ROM and Constant-Murley scores of both shoulders will be obtained, and the patient will complete the EQ-5D, 15D, DASH, and OSS questionnaires.

Should any adverse event demanding separate outpatient or inpatient care or surgery occur during the follow-up, an adverse event form will be completed within 24 hours of the execution of treatment. The information will be sent to the research coordinator. If the patient is not willing to continue in the study, or does not appear at appointments, or dies, a research discontinuation form will be completed. The study flow is outlined in Figure 1 and assessments and procedures are outlined in Table 1.

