### Power analysis

In Stratum I, when assuming an effect size of a 10-point difference in the DASH score and a standard deviation of 15 points, the estimated sample size is 37 patients (delta = 10, sd = 15, alpha = 0.05, power = 0.8). Thus Stratum I requires 74 patients (2 comparison groups). In Stratum II, when assuming an effect size of a 10-point difference in the DASH score and a standard deviation of 15 points, the estimated sample size is 66 patients (ANOVA, alpha = 0.05, power = 0.8). The number of comparison groups is three. The total number of patients in Stratum II is 198. Thus, the total number of patients in the study will be 272. We will assume a 10% drop-out rate in both groups; therefore, the total patient number required will be 299 (81 + 218). In cases in which the patient changes to a different treatment group, they will be analyzed according to the intention-to-treat principle. SD value has been estimated after Gummerson *et al.* (2003). The article describes the minimal detectable change in DASH as 10 points with an SD of 13 with a mean score of 15 points [28].

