### Time schedule

Recruiting time will be 3 years. The results will be analyzed after the 2-year follow-up period. The final report will be published by the end of the year 2017.

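### The primary outcome is DASH with no visit named, although three follow-up DASH scores precede the main analysis and Stratum I is sized for one test

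*Protocol article*

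**What the plan says.** The Hypothesis section fixes the instrument: "The primary outcome measure will be the Disabilities of the Arm, Shoulder and Hand (DASH) score". The Abstract repeats this. Neither gives a visit, and neither the Power analysis nor the Statistical analysis section adds one.

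On timing, the Follow-up section has a blinded examiner "perform a research examination at 6 months, and 1, 2, 5, and 10 years from the beginning of the treatment", and at these visits "the patient will complete the EQ-5D, 15D, DASH, and OSS questionnaires". Table 1 marks DASH before treatment and at 6 months, 1 year and 2 years. The Time schedule section says: "The results will be analyzed after the 2-year follow-up period".

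The Power analysis section sizes Stratum I with "delta = 10, sd = 15, alpha = 0.05, power = 0.8", giving 37 per group and 74 in total. It makes no allowance for more than one DASH test.

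For the main outcomes, the Statistical analysis section lists a t-test or a Mann–Whitney test according to skewness. It also lists regression, without naming an outcome, a visit or a time term.

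The Hypothesis section adds a secondary expectation about recovery: function improves during the first year, and "after 1 year significant improvement will be arrested".

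**The concern.** A primary endpoint is an instrument at a time. Here only the instrument is fixed, so the 10-point difference that the trial is powered for could be claimed at 6 months, 1 year or 2 years. Each choice answers a different question: speed of recovery at the early visit, final function at the late one. A result at whichever visit looks best could be presented as the primary result without departing from the text. The sample size and its 5% error rate assume that no such choice exists.

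This is more than detail left to an analysis plan. The visit is part of the trial's main question, and the article fixes every other element of the sample-size calculation (instrument, difference, SD, alpha and power).

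A smaller matter is attached. The plateau expectation is a claim of no further change, worded through significance, and no criterion is given for when improvement counts as arrested.

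**Working it through.** **Inputs from the protocol article.** Difference 10, SD 15, alpha 0.05, power 0.8, 37 per group (Power analysis). Three follow-up DASH visits by 2 years (Table 1). The 5- and 10-year visits fall after the main analysis and are not counted.

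**Assumed.** The correlation between DASH scores at different visits is not given. I take it as equal for all pairs and vary it from 0.5 to 0.9.

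**1. The protocol's own figure.** A two-sided two-sample t-test with effect size 10/15 = 0.667, alpha 0.05 and power 0.8 needs 36.3, so 37 per group. The stated figure reproduces. (The one-sided normal formula gives 28, so the stated alpha is evidently two-sided.) At 37 per group, power for one test at 0.05 is 0.81.

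**2. False-positive risk if any of the three visits may count.** With no true difference, the risk is P(max |Z| > 1.96) over three test statistics. If these were independent it would be 1 − 0.95³ = 0.143. With equal correlation, by simulation (2,000,000 draws):

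| Assumed correlation | Risk of at least one false positive |
|---|---|
| 0.5 | 0.126 |
| 0.6 | 0.118 |
| 0.7 | 0.109 |
| 0.8 | 0.098 |
| 0.9 | 0.084 |

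This is per two-group comparison, against a nominal 0.05.

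**3. Cost of correcting later.** Bonferroni over three visits tests each at 0.05/3 = 0.0167. With 37 per group the standardised difference is 10 / (15 × √(2/37)) = 2.87. The critical value is 2.39, so normal-approximation power is Φ(2.87 − 2.39) ≈ 0.68. The t-test gives 0.66. This is the power at any one given visit. Restoring 0.8 would need 49 per group (48.6 before rounding up) instead of 37.

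**4. The plateau expectation.** The 1-year and 2-year scores come from the same patients. With SD 15 at each visit, the SD of the change is 15 × √(2(1 − r)): 15.0 at r = 0.5 and 9.5 at r = 0.8. The 95% half-width is t × SD/√N:

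- Stratum I (N = 74): 3.5 points at r = 0.5, 2.2 at r = 0.8.
- Stratum II (N = 198): 2.1 points at r = 0.5, 1.3 at r = 0.8.

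The planned data can therefore estimate the change closely. An observed mean change only slightly larger than these half-widths would be significant, and a non-significant result would not by itself show that improvement had stopped.

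**The case against.** The strongest defence is that 2 years is the natural reading: the Abstract and Time schedule place the analysis after 2-year follow-up, and Table 1 ends there. This makes 2 years the sensible choice but does not make it the stated one. An analysis held after 2 years can still report 6-month or 1-year DASH as its main result, and the plateau expectation gives a ready argument for 1 year. It is also fair that the inflation arises only if the visit is chosen after seeing results, and that it shrinks as the correlation rises. The figures are what the text permits, not a prediction.

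A reader might infer more than the document supports:

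- *That only two-group tests at each visit are planned.* Regression and chi-square tests are also listed, ANOVA appears in the Stratum II power calculation, and nothing says that tests are run visit by visit.
- *That patients with partial follow-up will be dropped.* The article commits to intention to treat, and the handling of missing scores is commonly left to an analysis plan that is not shown.
- *That the plateau cannot be tested.* Paired 1- and 2-year scores will exist. What is missing is a method and a criterion, and an analysis plan could supply the method.
- *That the 10-point figure can serve as the plateau margin.* It is used as a between-group difference and described as a minimal detectable change, not as a margin for mean change over time.
- *That the strata can be pooled for the plateau.* The Objectives section says they are reported separately.

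**Conclusion.** The point holds in its narrow form and should be corrected. No section names the primary DASH visit, three follow-up scores exist by the main analysis, and Stratum I is sized for one test at 0.05. As written, the plan permits a false-positive risk of 8.4% to 12.6% per two-group comparison. That range rests on an assumed equal between-visit correlation of 0.9 to 0.5 and on free choice among the visits. Repairing it afterwards by Bonferroni would leave Stratum I with power of about 0.66 at a given visit, whereas naming one visit in advance keeps the planned 0.81 at no cost in patients.

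The plateau is a minor, secondary matter. The data can address it, but significance or its absence is the wrong criterion.

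**What to change.** Before any outcome is compared by treatment arm:

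1. Name one primary DASH visit and make the others secondary. Two years fits the stated analysis time.
2. Within each stratum, estimate the treatment contrast at that visit from a model that uses all follow-up DASH scores, in place of unadjusted t-tests or Mann–Whitney tests. One sound option is a mixed model for repeated measures with treatment by visit, baseline DASH and the age group used for the randomisation blocks. Stratum II has three arms, so naming the visit does not settle which pairwise contrasts are primary; state that as well.
3. Report the plateau as the within-patient change from 1 to 2 years with a 95% confidence interval, by stratum, against a margin stated and justified in advance. Do not carry over the 10-point between-group difference as that margin without justification.

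The cost is some wording, a little more programming and the loss of freedom to headline another visit. No extra data or patients are needed.

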### Objectives

The results of both strata will be analyzed and the results will be reported separately, as recommended by the CONSORT statement.

### Patients and methods

#### Inclusion criteria

• Low energy proximal humerus displaced (displacement more than 1 cm or 45 degrees) two-part fracture in which the fracture line emerges through the surgical (or anatomic) neck

• Low energy proximal humerus displaced (displacement more than 1 cm or 45 degrees) three- or four-part fracture

#### Exclusion criteria

• Refusal to participate in the study

• Under 60 years of age

• Not independent

• Dementia and/or institutionalized

• Does not understand written and spoken guidance in either Finnish or Swedish

• Pathologic fracture or a previous fracture of the same proximal humerus

• Alcoholism or drug addiction, e.g., in the emergency department, breathalyzer indicates blood alcohol concentration of more than 2 ‰

• Other injury to the same upper limb requiring surgery

• Major nerve injury (e.g., complete radial- or axillary nerve palsy)

• Rotator cuff tear arthropathy

• Open fracture

• Multi-trauma or -fractured patient

• Fracture dislocation or head-splitting fracture

• Non-displaced fracture

• Isolated fracture of the major or minor tubercle

• Gross displacement of the fracture fragments (no bony contact between fracture parts or the humerus shaft is in contact with the articular surface)

• Any medical condition that excludes surgical treatment

Patients with an x-ray verified proximal humerus fracture meeting the inclusion criteria will undergo a CT scan to assess the fracture classification. The scan area will include the entire scapula with the upper third of the humerus. Coronal, sagittal, and 3-dimensional volume reformats will be reconstructed. If the fracture meets the radiologic inclusion criteria, the patient will be invited to participate in the study. The patient will be informed of the study and will receive a written information sheet. When patients decide to participate in the study, they will be asked to fill-out a written informed consent form. The patients can withdraw from the study at any stage, on any grounds, and this will have no influence on the medical care given to the patients. If the patient is excluded from the study, information about age, sex, fracture type, reason for exclusion, medical condition, basic medication, and chosen treatment will be communicated to the research group using a case report form.

During hospitalization, the patient will be asked to fill out, with help if necessary, the EQ-5D, 15D, DASH, and OSS, and basic patient questionnaires with a VAS to determine their baseline characteristics. The patient's medical history, medication, and surgery will be recorded by a research nurse or researcher on a medical case report form. Potential primary complications will be recorded (e.g., nerve injury).

### Randomization

All patients will be randomized by a Tampere University Hospital research coordinator who will not attend the study. Patients with a two-part fracture will be randomized to either conservative or plate-fixation groups. Patients with multi-fragmented fractures will be randomized to conservative, plate fixation, or prosthesis groups. Both fracture types will be randomized using a random number matrix in block allocation fashion. The blocks will be age-dependent because, based on the literature, age and functional outcome are associated [27]. The treatment allocations from the matrix will be sealed in an envelope. After the patient's enrollment in the study has been confirmed, the research physician will contact the research coordinator, who will open the envelope and the randomized treatment will be carried out. The research coordinator will monitor the study flow. An independent monitoring committee has not been established.

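### Stratum II: adjusting the DASH comparisons for three- versus four-part CT class, already known at enrolment, would be a small and nearly free gain in precision

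*Protocol article*

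**What the plan says.** **Population.** Under Methods/Design, "Stratum II compares multi-fragmented fractures, including three- and four-part fractures".

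**Allocation.** Under Randomization, "Patients with a two-part fracture will be randomized to either conservative or plate-fixation groups", whereas "Patients with multi-fragmented fractures will be randomized to conservative, plate fixation, or prosthesis groups". Two-part and multi-fragmented fractures therefore have separate allocations, but three- and four-part fractures share one. The same section continues: "Both fracture types will be randomized using a random number matrix in block allocation fashion. The blocks will be age-dependent". The reason given is that age is associated with functional outcome.

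**When the class is known.** The text under Exclusion criteria says that patients with a qualifying fracture on x-ray "will undergo a CT scan to assess the fracture classification". This happens before they are invited to take part.

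**Reliability of the class.** Diagnosis and treatment says that in all classification systems "the intra- and inter-observer agreement are graded as poor or, at best, moderate".

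**Analysis.** Statistical analysis names the Mann–Whitney test for skewed main outcomes and the t-test otherwise. It also announces regression, without tying it to the primary comparison. Fracture group is one of several subgroup factors listed there, and Hypothesis says "Subgroup analysis will be performed in an effort to obtain limit values for specific treatments of different age and fracture groups". The term fracture group is not defined.

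**The concern.** Fracture class within Stratum II is a baseline feature that may predict DASH, and it is collected on every patient before allocation. Yet it enters neither the named blocking factor nor the named group test. Two things follow:

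- The three arms can differ by chance in their share of four-part fractures.
- Whatever DASH variance the class explains stays in the error term, so the intervals are somewhat wider than they need be.

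What is at stake is precision and the ease of reading a baseline table with a visible imbalance. The validity of the comparison is not at stake.

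**Working it through.** **Inputs from Power analysis.** 66 patients per arm in Stratum II (3 × 66 = 198), target difference 10 DASH points, SD 15. The 66 serves here only to set the size of chance imbalance. It does not follow from its own inputs: a three-group ANOVA at 80% power gives 34 per group for means 0, 0, 10 and 45 for means 0, 5, 10. That is a separate matter and errs towards a larger trial.

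**Assumptions, since the documents give no figures.** Four-part share q of 20–50%. DASH gap D between three- and four-part fractures of 5–10 points (up to 15 where stated). Class is taken as unrelated to age block.

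**1. Chance imbalance.** The SD of the difference in share between two arms is √(2q(1−q)/66). The largest gap among three arms was simulated as three binomial(66, q) counts.

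| q | SD between two arms (points) | P(largest gap > 10) | P(> 15) | P(> 20) |
|---|---|---|---|---|
| 0.2 | 7.0 | 33% | 10% | 1% |
| 0.3 | 8.0 | 43% | 17% | 3% |
| 0.4 | 8.5 | 48% | 21% | 4% |
| 0.5 | 8.7 | 49% | 22% | 5% |

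**2. Effect on a pairwise DASH contrast.** The SD of the shift is D × the SD above. For D = 10 this is 0.70 (q = 0.2) to 0.87 (q = 0.5) points; for D = 5 it is 0.35 to 0.44. The standard error of the contrast is 15 × √(2/66) = 2.61. The shift is already inside that figure. At q = 0.5 and D = 10, the within-class variance is 225 − 25 = 200, giving 200 × 2/66 = 6.06. The imbalance adds 0.87² = 0.76, and 6.06 + 0.76 = 6.82 = 2.61².

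**3. Type I error and power.** In simulations with q of 30% and 50% and D of 5, 10 and 15, the unadjusted t-test without balancing on class has a type I error of 4.6–5.0% and a power of 96.7–96.9% for a true difference of 10.

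Conditional on an imbalance that has occurred, the error is not exactly 5%. Take q = 0.5, D = 10 and a 15-point imbalance. The shift is 1.5, the within-class standard error is √6.06 = 2.46, and the rejection limit is 1.96 × 2.61 = 5.12. Then P(Z > (5.12 − 1.5)/2.46) + P(Z > (5.12 + 1.5)/2.46) = 7.1% + 0.4%, or about 7.4% from unrounded terms. With D = 5 the corresponding figure is about 5.6%.

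**4. Gain from adjusting.** The variance share explained is q(1−q)D²/225, and the equivalent gain in sample size is 1/(1 − share) − 1. To allow for classification error, assume that the recorded class correlates 0.6 with the true class, so that the share is multiplied by 0.36.

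| q | D | Share | Gain, error-free class | Gain, correlation 0.6 |
|---|---|---|---|---|
| 0.5 | 10 | 0.111 | 12.5% | 4.2% |
| 0.5 | 5 | 0.028 | 2.9% | 1.0% |
| 0.2 | 10 | 0.071 | 7.7% | 2.6% |
| 0.2 | 5 | 0.018 | 1.8% | 0.6% |

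Without stratified lists, adjusting costs on average 0.8% in variance (3% at the 95th percentile). At the bottom of the table the net gain is therefore about nil. At the top (q = 0.5, D = 10, error-free class), power for a difference of 10 rises from about 96.9% to Φ(10/2.46 − 1.96) ≈ 98%.

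**5. Subgroup power.** For a 10-point effect among four-part fractures at q = 20%, 30%, 40% and 50%, power is 40%, 56%, 68% and 77% with perfect balance, and 39%, 55%, 67% and 77% on average without it.

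**The case against.** The strongest reply is that nothing here is wrong. Randomisation makes any difference in severity random, the standard error already contains it, and power at 66 per arm is about 97% before any adjustment. Regression is announced, and a condensed article may leave its covariates, and any further blocking factors, to a fuller document. No DASH gap between the classes is given, and the protocol itself doubts the reliability of the classification. All of this stands, and it is why the point is minor. It does not remove the point: the group comparison that the article does state is unadjusted, and naming the class in advance avoids choosing it after an imbalance has been seen.

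A reader might infer more than the documents support:

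- **That fracture type is ignored in allocation.** It is not: two-part and multi-fragmented fractures are allocated separately. Age stands alone only within Stratum II.
- **That the cited trials show the classes must be kept apart.** Previous studies describes one trial in three-part fractures and one in four-part fractures, but also one that enrolled both together, which is a precedent for pooling.
- **That a promised three- versus four-part comparison is undermined.** Fracture group is never defined that way, the subgroup aim is exploratory, and treatment remains randomised within each class. The number of four-part patients limits that analysis, and stratifying does not change it.

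**Conclusion.** The point holds as a minor precision improvement. Stratum II allocates and, by its stated tests, compares arms without using a baseline class that is already collected. Visible imbalance is common: the largest gap exceeds 10 percentage points in about a third to a half of trials. Its effect is small: an SD of at most about 0.9 DASH points at an assumed 10-point gap, against a standard error of 2.6. A reader might call this bias or an inflated error rate. It is neither: the overall type I error is kept, and only the error conditional on a large observed imbalance departs from 5%.

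The gain from adjusting is roughly 1–12% in equivalent sample size. This rests on the assumed gap of 5–10 points, the assumed share of 20–50%, and how well the CT reading captures the true class. With imperfect classification the lower values apply, and in the least favourable case the gain is about nil.

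**What to change.** For the Stratum II DASH comparisons, prespecify a regression (ANCOVA) model with treatment, age block and three- versus four-part CT class as terms. Use the class recorded at enrolment, whatever is found later. Define fracture group as that class for Stratum II, so that the subgroup analysis and the model use the same variable.

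If recruitment has not begun, separate age-blocked lists for the two classes are an option. They should come with the model term: in the simulations, balancing on class while keeping the unadjusted t-test made the test conservative (type I error 2.4–4.9%). If lists are already in use, leave them and adjust only.

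The CT is done on every patient, so the cost is one model term: under 1% in variance on average if the class turns out not to be prognostic. Optional lists would add a set of envelopes and a few more incomplete blocks. Imperfect agreement on the class reduces the gain but introduces no bias.
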